#### Data management and confidentiality

In this trial, all data will be entered into the computer and several databases will be established. Modifications to data of the database will be documented. Moreover, data management personnel will use the mobile hard disk to back up the data of the databases once a month. Statisticians and supervisors will conduct regular data verification.

All written materials concerning to the study, including informed consent, medical history, surgical records, etc., will be securely stored in file cabinets. All random assignment, data collection, and follow-up management containing participant information will be conducted in the form of a web spreadsheet, which can only be accessed and edited with specific permissions. Participants' information will not be disclosed outside of this study without their written consent.

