**Method:**

The SWEET study is a randomized, controlled, single-blind, single-center non-inferiority trial with two parallel groups in two cohorts respectively. After eligibility screening, subjects who meet the inclusion criteria will be divided into Cohort EVAR or Cohort TEVAR according to clinic interviews. And then participants in two cohorts will be randomly allocated to either intervention groups receiving percutaneous access endovascular repair or controlled groups receiving cutdown access endovascular repair separately. Primary clinician-reported outcome (ClinRO) is access-related complication, and primary patient-centered outcome (PCO) is time back to normal life. Follow-up will be conducted at 2 weeks, 1 month, 3 months postoperatively.

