### Assignment of intervention

Cohort EVAR and TEVAR in the SWEET trial are designed as a parallel randomized controlled, single-blind, single-center non-inferiority trial in a 1:1 ratio. The flow diagram for the study is outlined in Figure 1. After eligibility screening, eligible subjects in the two cohorts will be randomly allocated to either intervention groups receiving percutaneous access endovascular aortic repair or control groups receiving cutdown access endovascular aortic repair separately. As for patients who require brachial artery access in Cohort TEVAR, the assignment will be based on their femoral artery access, independent of the approach for upper extremity access.

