**Figure 1 F1:**
[figure not shown]
Flow of participants randomly assigned to percutaneous groups and cutdown groups.

Block randomization stratified by age and body mass index (BMI) using permuted blocks of random sizes will be performed with 1:1 allocation in both cohorts. Randomization sequence is generated by SPSS 26.0 statistical software by a biostatistician. The block size will be concealed until the primary endpoints are analyzed. An independent research coordinator will be responsible for keeping the sequentially numbered allocation sequence list, and will inform the surgeons about the assigned access procedure prior to intervention. To avoid performance bias, every surgeon must have had 10 or more ProGlide procedures, and experience of at least 20 surgical cutdowns to expose the access artery is also needed.

Obviously, trial participants and operating team cannot be blinded to the allocation. The data will be entered into the computer in separate tables by employees outside the research team so that the analysts can analyze data without knowing the allocation information. Therefore, only data analysts are blinded in this study.

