#### Primary outcomes

The primary ClinRO endpoint is access-related complications assessed in-hospital, 2 weeks and 1 month after surgery. The definition of access-related complications includes

Access-site infection: inflammation of the groin presenting redness, swelling or exudation and requiring consecutive oral or intravenous antibiotics therapy.Bleeding/hematoma: fresh oozing blood or old blood stains seen on wound dressing/blood accumulation around the access site.Access-related arterial injury: arterial injuries requiring endarterectomy or patching due to the access technique.Femoral artery occlusion: femoral artery thrombosis presenting as distal artery pulse poorly requiring thrombectomy.Pseudoaneurysm: false aneurysm at the site of arterial injury presenting as a painful and pulsatile mass.Lymphorrhagia/seroma: swelling at access site caused by damage to lymphatic duct during access obtaining.Access-related nerve injury: nerve injuries presenting as persistent paresthesia of the thigh due to the access technique.Wound dehiscence: a partial or complete separation of previously close access wound edges.

The primary PCO endpoint is time (days) back to normal life/work assessed at 2 weeks by telephone interview and checked at 1 month and 3 months in outpatient clinics after surgery. To determine the outcomes that patients care most, we conducted a preliminary survey in 50 patients who received EVAR or TEVAR prior to our trial, and recovery time back to normal life or work represented the major PCO endpoint.

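### The reason given for blinding only the data analysts does not cover the telephone interviewer for the primary patient-centered outcome, and 'single-blind' does not tell readers who is masked

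*Protocol article*

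**What the plan says.** All references are to the protocol article.

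- **Label.** The Method paragraph of the abstract describes a "randomized, controlled, single-blind, single-center non-inferiority trial". Assignment of intervention repeats the label: each cohort is "designed as a parallel randomized controlled, single-blind, single-center non-inferiority trial in a 1:1 ratio". Neither sentence says who is masked.
- **Who is masked.** The blinding paragraph of Assignment of intervention, after Figure 1, says: "Obviously, trial participants and operating team cannot be blinded to the allocation". Data are to be entered in separate tables by employees from outside the research team, so that analysts do not learn the allocation. The paragraph ends: "Therefore, only data analysts are blinded in this study".
- **Primary patient-centered outcome.** Under Primary outcomes, this is the number of days until return to normal life or work, "assessed at 2 weeks by telephone interview and checked at 1 month and 3 months in outpatient clinics after surgery". No section says who makes the call.
- **Data handling.** Data management and confidentiality says: "All random assignment, data collection, and follow-up management containing participant information will be conducted in the form of a web spreadsheet". The rest of that sentence limits access and editing to holders of specific permissions. The same section adds: "Statisticians and supervisors will conduct regular data verification".

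**The concern.** The blinding paragraph moves from two groups that cannot be masked (participants and the operating team) to the statement that analysts alone are masked. Outcome assessors are a third group. They are left unmasked without a reason that applies to them.

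This matters most for the primary patient-centered outcome. Return to normal life or work is self-reported, the article gives no criterion for when it has been reached, and participants know which access they had. An interviewer who also knows the arm, and who expects faster recovery after a puncture than after a groin incision, could move the reported date by the way the question is put. Blinding the analysts cannot correct this, because it acts only after the value has been recorded.

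The label adds a smaller problem. A reader who sees only the abstract learns that the trial is single-blind. That reader could suppose that patients or assessors are masked, when neither is.

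**Working it through.** The article gives no figure on this point, so there is nothing to recompute. The check sets the statements side by side.

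1. **Does the stated reason cover every unmasked group?**
   - Participants: yes. They know whether they have a 5-cm groin incision or a puncture (Intervention).
   - Operating team: yes. They carry out the access.
   - Staff examining the wound for access-related complications at ward rounds and dressing changes (Data collection methods): not named, but the wound shows the arm, so masking them would be hard in practice.
   - The 2-week telephone interviewer: no. The outcome is a number of days reported by voice, and recording it requires neither sight of the wound nor knowledge of the procedure.

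2. **Is a masked interviewer merely unmentioned, or excluded?** Excluded. The word 'only' in the blinding statement leaves no room for a masked caller. This is therefore something the article states, and not a detail left to a fuller document.

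3. **How far would masking the call reach?** Table 1 of the article has the outcome assessed at 2 weeks, 1 month and 3 months. Primary outcomes places the two later checks in outpatient clinics. For a patient who has not resumed normal life by 2 weeks, the value can only be set at a clinic visit. The article does not say what share that will be. Masking the first call alone thus protects only part of the data, which is why the later checks need the same scripted question.

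4. **How large could the bias be?** It cannot be derived. Sample size states that no earlier studies reported patient-centered outcomes and bases the calculation on access-site complications. There is no expected mean, standard deviation or target difference in days against which to set an interviewer effect. What can be stated is the scope: one of the two primary endpoints, in both cohorts, 120 + 100 = 220 planned patients.

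5. **Does the data-management section break the analyst blind?**
   - Assignment of intervention gives the sequence list to an independent coordinator and uses separate tables entered by outside employees.
   - Data management and confidentiality names a web spreadsheet as the medium, restricts access and editing by permission, and also says that several databases will be set up.
   - No sentence gives analysts, enrolling staff or interviewers permission to see assignments.
   - The statisticians who verify data are not said to be the blinded analysts. The article also mentions a biostatistician who generates the sequence and an independent statistician for the interim analysis.

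   These statements can all be true together, so there is no contradiction.

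**The case against.** The best defence is that the design is disclosed. Assignment of intervention says plainly that patients and operators know the arm and that analysts alone are masked, so the full text defines what single-blind means here. That stands. The article does not conceal its open-label collection, and the label is imprecise only where it appears without that explanation.

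It can also be said that masking the caller achieves little. Participants may reveal their arm during the call, and the value is checked again in clinics with no masking. This stands as a limit on the benefit. It does not justify leaving the interviewer informed when masking the call costs almost nothing.

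A third objection is that the article does not show that suitable staff exist. The research nurse appears only as the person who gives consent information, and nothing says that the nurse is unaware of the allocation. This also stands in part: using existing staff is an assumption that the trial team must confirm.

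A reader might go further and infer that the shared spreadsheet, together with regular verification by statisticians, defeats the analyst blind or exposes upcoming assignments to those who enrol. The article does not support this. Access is restricted by permission, the sequence list has an independent holder, block sizes are random and concealed, and no passage opens the assignments to analysts or enrolling staff. Who holds which permission is operational detail that an article may leave to the full protocol.

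**Conclusion.** The point holds in a limited form. By stating that analysts alone are blinded, the article leaves the interviewer for a self-reported primary outcome unmasked, and the reason it gives does not apply to that person. The single-blind label in the abstract and under Assignment of intervention does not convey that neither participants nor assessors are masked.

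The likely direction is towards percutaneous access, on the assumption that interviewers expect the less invasive route to give faster recovery. No size can be given. The conclusion rests on reading 'only' literally and on the 2-week telephone interview needing no wound inspection to record the return date.

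It does not extend to the data-management section, which is compatible with the analyst blind. Nor does it extend to a simple remedy for access-related complications, since wound inspection reveals the arm. This is an inexpensive improvement to the design and a correction of wording. It is not a flaw that invalidates the trial.

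**What to change.** 1. **Assignment of intervention and Primary outcomes:** state that the 2-week call is made by existing staff outside the operating team who are not told the allocation. Candidates are the outside-team employees already planned for data entry, if they are not shown the assignment, or a research nurse who is not told the arm.
2. **Primary outcomes:** specify a fixed script that asks for the date of return to normal life or work before any question about the wound. Use the same scripted question at the 1-month and 3-month checks.
3. **Abstract (Method) and Assignment of intervention:** replace single-blind with 'open-label with blinded data analysts', and revise the sentence on who is blinded to include the 2-week interviewer.
4. **Data management and confidentiality (optional clarification):** add one sentence saying that assignment is kept apart from outcome data and is not shown to the statisticians who verify them.

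The cost is some scheduling work, a short script and a less favourable blinding label. No extra visits are needed. Extra staff should not be needed either, provided that someone already on hand can be kept unaware of the arm. Protection remains partial, because participants know their arm and may reveal it, and the later checks take place in clinics without masking.

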### Statistical methods

#### Analysis population

As Cohort EVAR and Cohort TEVAR were powered and randomized separately, the statistical analysis of both cohorts is planned to be reported separately. The analysis populations of this trial involve modified intention-to-treat (ITT) and per-protocol (PP) populations. The modified ITT is determined after randomization and when the patient started endovascular aortic repair, hence all patients who indeed receive endovascular aortic repair are involved in the primary analysis within the respective access group as originally allocated. In this trial, the modified ITT will be the main analysis set for the summary of both ClinROs and PCOs data. Both ITT and PP analysis are required for test of non-inferiority, and PP analysis serves as a sensitivity analysis. The non-inferiority margin was predetermined at 10%, and the non-inferiority test will be evaluated as a two-sided test at alpha = 0.05. When non-inferiority is reached, ITT is further tested for superiority.

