#### Sample size

As no previous studies reported PCOs, we used the incidence of access site complications to estimate the sample size of the SWEET trial. According to previous studies, the incidence of access site complications in percutaneous EVAR was 7.64%, compared with 11.81% in cutdown EVAR (13). We estimated the number of patients needed in this non-inferiority trial with non-inferiority margin of 0.10 (bilateral α 5%, power 80%) by PASS 15.0 software, and 54 patients are required for percutaneous and cutdown EVAR group, respectively. To allow for 10% drop out, 60 patients will be recruited per group, i.e., 120 for Cohort EVAR.

Previous TEVAR studies lacked solid data in above aspects, however, the relevant data of transcatheter aortic valve implantation (TAVI) can be used for reference due to their similar surgical approach (15). The incidence of access site complications was 8.7% in percutaneous TAVI and 8.5% in cutdown TAVI (16). The sample size was calculated with non-inferiority margin of 0.15 (bilateral α 5 %, power 80 %), 45 patients are required for percutaneous and cutdown TEVAR group separately. Fifty patients will be recruited each group allowing for 10% drop out, and the number of subjects in Cohort TEVAR is 100. Therefore, the total sample size of the SWEET trial is 220. The whole calculation process can be found in Supplementary Tables S3, S4 (Supplementary Material).

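### Cohort TEVAR has two non-inferiority margins: 15 points where it is sized and 10% where the analysis is defined; power at 10 points is about 38% to 54%, not 80%

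*Protocol article*

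**What the plan says.** The Sample size section of the protocol article treats the cohorts separately. Cohort EVAR is planned as a "non-inferiority trial with non-inferiority margin of 0.10", with "bilateral α 5%, power 80" per cent. For Cohort TEVAR, "The sample size was calculated with non-inferiority margin of 0.15", with the same alpha and power. The TEVAR rates are borrowed from transcatheter valve studies: "The incidence of access site complications was 8.7% in percutaneous TAVI and 8.5% in cutdown TAVI". The result is that "45 patients are required for percutaneous and cutdown TEVAR group separately", and "Fifty patients will be recruited each group allowing for 10% drop out".

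The Analysis population section begins by noting that the two cohorts have their own sizing and randomisation and will be reported apart. It then gives one rule without naming a cohort: "The non-inferiority margin was predetermined at 10" per cent, and "the non-inferiority test will be evaluated as a two-sided test at alpha = 0.05". It does not mention 15 points and does not limit the 10% to EVAR.

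**The concern.** The margin is the decision rule for the primary clinician-reported endpoint. For Cohort TEVAR, an upper confidence limit between 10 and 15 points means non-inferior under the Sample size section and not non-inferior under the Analysis population section. A reader of the final report could not tell which rule had been fixed in advance.

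The stated power is also at stake. If the analysis section is applied as written, TEVAR is tested against a margin that its sample size was never computed for.

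Timing adds to this. The Data monitoring section plans an interim analysis of the primary outcomes once half the participants have been randomised and followed for 3 months. The Protocol amendments section lists changes to sample size and statistical methods as possible amendments. An ambiguity still open at that point would be hard to settle credibly.

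**Working it through.** **Inputs.** From Sample size: TEVAR rates pT = 0.087 and pC = 0.085, margin m = 0.15, two-sided alpha 5%, power 80%, 45 per group (50 recruited). From Analysis population: m = 0.10, two-sided alpha 5%. All figures are per patient, as in the protocol's own sizing, and use the unpooled normal approximation.

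**Formulas.**
- Variance sum V = pT(1 − pT) + pC(1 − pC) = 0.0794 + 0.0778 = 0.1572
- n per group = (z_α + z_0.80)² × V / (m − (pT − pC))²
- SE = √(V/n)
- Power = Φ((m − (pT − pC))/SE − z_α)

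A two-sided 5% test corresponds to z_α = 1.96 against the margin; a one-sided 5% test to 1.645. The planned difference pT − pC is 0.002.

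**Step 1: reproduce the plan's 45 (m = 0.15).**
- One-sided 5%: (1.645 + 0.842)² × 0.1572 / 0.148² = 44.4, so 45 per group, and 45/0.9 = 50. This matches.
- Stated two-sided 5%: (1.960 + 0.842)² × 0.1572 / 0.148² = 56.3, so 57 per group, and 57/0.9 gives 64 after dropout. This does not match.

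EVAR behaves the same way: its 54 per group is obtained at one-sided 5%, against 69 at two-sided 5%. The published sizes therefore rest on a looser alpha than the text states.

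**Step 2: does the margin change the conclusion?** With 45 per group, SE = √(0.1572/45) = 5.91 points. If the planned rates are observed, the upper 95% limit is 0.2 + 1.96 × 5.91 = 11.8 points. With 50 per group, SE = 5.61 and the limit is 0.2 + 1.96 × 5.61 = 11.2 points. Both lie between 10 and 15.

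**Step 3: power.** For 45 per group and m = 0.10 at two-sided 5%: 0.098/0.0591 − 1.96 = −0.30, and Φ(−0.30) = 38%. The other cells follow in the same way.

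| Margin | Alpha | 45 per group | 50 per group | n per group for 80% (after 10% dropout) |
|---|---|---|---|---|
| 15 points | two-sided 5% (stated) | 71% | 75% | 57 (64) |
| 15 points | one-sided 5% | 80% | 84% | 45 (50) |
| 10 points | two-sided 5% (stated) | 38% | 42% | 129 (144) |
| 10 points | one-sided 5% | 51% | 54% | 102 (114) |

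**Step 4: sensitivity to method.** At 10 points, 45 per group and two-sided 5%, exact enumeration of the unpooled test gives 39.7%, and the Farrington-Manning test about 31% to 32%. The choice of test does not rescue the power.

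**Step 5: what each margin tolerates.** Against an 8.5% cutdown rate, 10 points allows up to 18.5% (18.5/8.5 = 2.2-fold) and 15 points up to 23.5% (23.5/8.5 = 2.8-fold).

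**The case against.** The best defence is that this is a drafting omission. The Analysis population section itself says that the cohorts were sized separately, so a cohort-specific margin may have been intended, with the 10% written for EVAR only. That is plausible, but the text does not say so. Supplementary Tables S3 and S4 are not shown. They are described as holding the sample size calculation, so they might confirm the 15 points, but that would not remove the 10% from the analysis section.

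Three further points limit how far the criticism goes.

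- **The 38% is not the effect of the margin alone.** A reader might infer that moving from 15 to 10 points takes power from 80% to 38%. It does not. At the stated two-sided 5%, power with 45 per group is already about 71% at 15 points; the margin takes it from there to 38%. At the one-sided 5% that reproduces the 45, the margin takes it from 80% to about 51%. At that alpha the upper limit in Step 2 would be 0.2 + 1.645 × 5.91 = 9.9 points, just inside 10, so the reversal shown there belongs to the stated two-sided test.
- **The analysis is not per patient.** The section on analysis of primary and secondary outcomes counts complications per femoral access. That could change the effective sample size, but the article gives neither the number of accesses per patient nor their correlation, so the amount cannot be calculated.
- **A reader might infer that the margin will be picked after the results are known.** The article does not support that. It states that data analysts are blinded and that major amendments go to the ethics committee. The ambiguity leaves the possibility open; it is not evidence of intent.

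None of these removes the contradiction or brings power at 10 points near 80%.

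**Conclusion.** The contradiction stands. Cohort TEVAR has two incompatible margins, and under the trial's own planning rates and stated alpha the conclusion depends on which section is followed. Power at 10 points is about 38% to 42% at two-sided 5%, or about 50% to 54% at one-sided 5%, for 45 to 50 patients per group. These figures assume the borrowed rates of 8.7% and 8.5%, one observation per patient and the unpooled approximation.

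The article does not show which margin is correct. Having been used for the sample size does not justify 15 points, and appearing in the analysis section does not justify 10.

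**What to change.** Before any comparative data are seen, including the interim analysis:

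1. In Analysis population, state one margin for each cohort and justify it, including the complication rate it tolerates (for TEVAR, 8.5% up to 23.5% at 15 points, or up to 18.5% at 10).
2. Make Sample size agree with it.
3. Restate TEVAR power for that margin at the alpha actually used. With 45 per group at two-sided 5%, this is about 71% at 15 points or about 38% at 10 points. Writing 15 points into the analysis section without correcting the 80% would leave an error in place.
4. Label the power as per patient, or give the assumptions about accesses per patient needed to compute it per access.

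The cost is a text amendment, a registry update and a less favourable stated power. No patients are added if the sponsor accepts that power. Restoring 80% at two-sided 5% would need 57 per group (64 recruited) at 15 points or 129 per group (144 recruited) at 10 points, against the 50 now planned.
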